# Health consequences for mother and baby of substantial pre-conception weight loss in obese women: study protocol for a randomized controlled trial

**DOI:** 10.1186/s13063-018-2615-6

**Published:** 2018-04-24

**Keywords:** Pregnancy, Pre-conception, Obesity, Weight loss, Glucose metabolism, Pregnancy outcomes, Randomized trial

## Abstract

**Background:**

Current guidelines for the management of obesity in women planning pregnancy suggest lifestyle modification before conception. However, there is little evidence that lifestyle modification alters pregnancy outcomes. Bariatric surgery results in significant weight loss. This appears to reduce the risk of adverse pregnancy outcomes for the mother but may increase the risk of adverse outcomes for the infant. In order to reduce the risks of obesity-related adverse pregnancy outcomes for both mother and offspring, alternative approaches to the management of obesity in women planning pregnancy are needed.

**Methods/design:**

This study, a two-arm, parallel group, randomized control trial, will be conducted at the Metabolic Disorders Centre, University of Melbourne. This trial will recruit 164 women aged 18–38 years with a body mass index of 30–55 kg/m^2^ who plan to conceive in the next 6–12 months. Women will be randomized to one of two 12-week interventions (Group A and Group B). Group A will aim for modest weight loss (MWL; ≤ 3% body weight) using a hypocaloric diet. Group B will aim for substantial weight loss (SWL; 10–15% body weight) using a modified very low energy diet (VLED) program. All participants will be asked to comply with National Health and Medical Research Council (NHMRC) guidelines for exercise and will be provided with standard pre-pregnancy advice according to Royal Australian and New Zealand College of Obstetrics and Gynaecology guidelines. All participants will then be observed for the subsequent 12 months. If pregnancy occurs within the 12-month follow-up period, data on weight and metabolic status of the mother, and pregnancy outcomes of mother and offspring will be recorded.

The primary outcome is maternal fasting plasma glucose at 26–28 weeks’ gestation, given that this is known to correlate with pregnancy outcomes. Time to conception, live birth rate, gestational weight gain, and a composite of adverse pregnancy outcomes for mother and baby will comprise the secondary outcomes.

**Discussion:**

There is increasing emphasis on obese women losing weight before conception. To date, no randomized controlled trial has demonstrated an effective means of weight loss that results in improved pregnancy outcomes for both mother and baby. This study intends to determine if substantial pre-conception weight loss, achieved using a VLED, improves pregnancy outcomes for mother and baby when compared with standard care. This research will potentially change clinical care of an obese woman planning pregnancy.

**Trial registration:**

ANZCTR, 12,614,001,160,628. Registered on 5 November 2014.

**Electronic supplementary material:**

The online version of this article (10.1186/s13063-018-2615-6) contains supplementary material, which is available to authorized users.

## Background

Obesity is present in one in three women of child-bearing age [1]. Currently, guidelines for the management of obesity in women planning pregnancy are based on consensus view and lack supporting evidence. It is critically important that we have evidence-based weight loss tools that reduce the risk of obesity-related pregnancy outcomes for both mother and fetus. This study aims to determine if substantial weight loss achieved using a modified very low energy diet (VLED) program fulfils this clinical need.

The impact of maternal obesity on pregnancy outcomes have been well described. Maternal risks include gestational diabetes, gestational hypertension and pre-eclampsia, medically indicated induction of labor, instrumental delivery, and primary Cesarean section [1]. Fetal risks include large-for-gestational age (LGA), pre-term delivery, hyperbilirubinemia, hypoglycemia, and need for admission to the special care nursery or intensive care unit [1, 2]. Maternal obesity also increases the risk of congenital anomalies [3, 4] and perinatal death [5, 6].

Pre-gravid maternal obesity [7], maternal gestational diabetes (GDM) [7], and being born LGA [8] are the most significant risk factors for obesity in childhood. Obesity in childhood is the strongest predictor of obesity in adulthood [9]. Emerging evidence suggests the metabolic status of the mother may “program” the offspring’s long-term risk of metabolic disease [10–12].

To date, studies aimed at reducing obesity-related adverse pregnancy outcomes have focused on limiting gestational weight gain. More than 50 such interventional trials have been conducted but these studies have, at best, been only very modestly effective in reducing adverse pregnancy outcomes. The LIMIT study was a large, well-designed study of lifestyle modification during pregnancy. The study demonstrated no risk reduction for delivering a baby ≥ 90th centile for gestational age and no improvement in maternal pregnancy or birth outcomes. There was also no statistically significant difference in gestational weight gain between the control and intervention groups [13]. Similarly, the UPBEAT trial showed that a program of diet and exercise had no impact on the risk of gestational diabetes and LGA offspring in obese pregnant women [14]. These important studies inform us that alternative approaches to the management of obesity in women planning pregnancy are needed.

A review of five national guidelines from Canada, Ireland, the United Kingdom, Australia/ New Zealand, and the United States of America showed that there are significant differences in the management of obese women planning pregnancy between countries [15]. All guidelines included in the review recommend weight loss before pregnancy using lifestyle modification such as diet and exercise. These recommendations are made on the basis of consensus opinion. The United Kingdom guidelines offer specific advice on how to monitor weight and change health behavior, including the recommendation to reach a body mass index (BMI) of 18.5–24.9 kg/m^2^ before conception [15]. However, for a woman of average height (165 cm) and a BMI of 40 kg/m^2^, a 42-kg weight loss would be required to reach BMI 24.9 kg/m^2^. Lifestyle modification in the Counterweight Programme (*n* = 642) demonstrated a mean weight loss of 3.0 kg after 12 months [16]. Similarly, a lifestyle program in obese infertile women (*n* = 236) demonstrated a mean weight loss of 4.4 ± 5.8 kg over six months [17]. While modest weight loss has metabolic benefits for the woman [18–20], there is no evidence that it reduces the risk of obesity-related pregnancy complications.

Numerous retrospective studies of bariatric surgery before conception have demonstrated a reduction in adverse pregnancy outcomes for the mother [21–25]. The largest study (*n* = 627) demonstrated that bariatric surgery (mean weight loss from surgery to early pregnancy = 37 kg [BMI 43.7 kg/m^2^ to 30.3 kg/m^2^]) was associated with a reduction in maternal gestational diabetes and LGA infants. However, risk of small-for-gestational-age (SGA) infants and possibly perinatal mortality was increased [26]. In this study, the median interval from surgery to conception was 12 months, suggesting that even after conception, rapid surgery-induced weight loss was occurring. Catalano has shown that those women who gain inadequate weight during pregnancy (< 5 kg) have a significantly increased risk of SGA infants [27]. SGA infants are at similar long-term risk of metabolic disease to LGA infants [27].

There is limited experience with the use of medications such as sibutramine, phentermine, and orlistat as an adjunct to lifestyle modification in the pre-pregnancy setting [28, 29]. In these studies, slightly more weight loss was achieved when the medication was used. However, live birth rate was not substantially improved. There are no published studies examining the impact of GLP-1 analogs in the pre-pregnancy setting. However, case studies of inadvertent use of GLP-1 analogs in the pre-pregnancy and early pregnancy setting do exist and no adverse outcomes are reported [30]. This is an area of future potential research [31, 32].

VLEDs result in 10–15% weight loss over 12 weeks in an adult population [33]. Such programs may be particularly suitable for pre-conception weight loss as they promote rapid weight loss which assists program engagement [34], induce sufficient weight loss to improve fertility [35, 36], ensure adequate intake of protein which is associated with favorable pregnancy outcomes if pregnancy occurs [37], and can be stopped before conception, ensuring gestational weight gain is not affected. Some have argued that VLEDs should not be used in women planning pregnancy due to the potential of exposing the developing fetus to ketosis. This concern has been based on animal studies, which show potential harm to the pup when exposed to high-level ketosis for the entire period of gestation and lactation [38]. Women on VLED programs are advised to use contraception. Hence, the early developing fetus would only be exposed to ketosis if unintended pregnancy occurred. Reassuringly, the human fetus is regularly exposed to brief periods of ketosis in the context of hyperemesis gravidarum [39], type 1 diabetes [40], and normal pregnancy [41]. In all such cases, there is no evidence of harm to the fetus. Multiple small studies of VLED pre-pregnancy support this concept [42, 43].

The primary metabolic abnormalities associated with obesity are insulin resistance and hyperinsulinemia [44]. Insulin resistance not only affects glucose metabolism; increased free fatty acids and triglycerides are hallmarks of insulin resistance. The obese woman begins pregnancy with greater insulin resistance than her normal weight counterpart. There is a further 50–60% increase in insulin resistance due to the pregnancy itself [45]. This progressively increases as the pregnancy progresses [46]. If the beta cell cannot compensate for the increase in insulin resistance, glucose levels rise. The developing fetoplacental unit is exposed to these metabolic changes [47].

The seminal Hyperglycaemia and Adverse Pregnancy Outcome (HAPO) study (*n* = 23,316) demonstrated that even within the “normoglycemic” range, small increases in maternal glucose are associated with adverse pregnancy outcomes [48]. Similarly, a small decrease in maternal glucose is associated with a lower risk of adverse pregnancy outcomes. For example, a reduction in maternal fasting glucose from glucose category 5 (5.0–5.2 mmol/L) to glucose category 3 (4.5–4.7 mmol/L) (a 10% reduction in fasting glucose) will result in a reduction in the rate of neonates born LGA from 16.5% to 10.1%, cord blood C-peptide from 17.7% to 8.2%, and the rate of primary Cesarean section from 23.7% to 18.5% [48].

The HAPO data were re-analyzed to investigate the impact of BMI on adverse pregnancy outcomes [49]. This study demonstrated that both maternal hyperglycemia and obesity at 24–32 weeks’ gestation are independently associated with adverse pregnancy outcomes. However, the combination has a greater impact than either one alone. The same association exists if pre-pregnancy BMI (based on patient recall) is considered. Weight loss improves glycemic control [19, 20]. Pre-pregnancy weight reduction has the potential to improve pregnancy outcomes, directly through weight loss and indirectly through improved glycemic control.

Regardless of the method of weight loss, the counter-regulatory responses to weight loss will result in a tendency to weight regain [50]. While any weight regain is not ideal, multiple studies suggest that weight maintenance for 12 months is possible [51, 52]. Importantly, the rate of weight regain is not altered by the rate of weight loss [34]. This would allow a window for conception at a time of lower weight.

In considering weight loss in an obese woman before pregnancy, we must identify a weight loss target that both increases fertility and decreases the risks of adverse pregnancy outcomes due to obesity. This study aims to address this need by exploring the impact of substantial pre-conception weight loss in obese woman on maternal and fetal pregnancy outcomes.

### Aim

Primary aim: To determine if non-surgical substantial pre-conception weight loss (10–15% body weight) in obese (BMI ≥ 30 kg/m^2^) women causes a ≥ 10% reduction in fasting glucose at 26–28 weeks’ gestation when compared with modest pre-conception weight loss (≤ 3% body weight loss).

Secondary aims:

The secondary aims of the study are to determine if, in obese women (BMI ≥ 30 kg/m^2^), non-surgical substantial pre-conception weight loss (10–15% body weight) when compared with modest pre-conception weight loss (≤ 3% body weight), results in:A reduction in the composite end point of maternal gestational diabetes (IADPSG definition), LGA, intrauterine growth restriction (IUGR), gestational hypertension/pre-eclampsia, delivery before 37 weeks’ gestation, primary Cesarean section, shoulder dystocia/birth injury, neonatal hypoglycemia, neonatal hyperbilirubinemia, neonatal special care nursery, or intensive care admission.A reduction in the rate of maternal gestational diabetes (IADPSG definition).A reduction in the rate of LGA infants.A reduction in the rate of IUGR.A reduction in the rate of gestational hypertension/pre-eclampsia.A reduction in the rate of delivery before 37 weeks’ gestation.A reduction in the rate of primary Cesarean section.A reduction in the rate of birth injury/shoulder dystocia.A reduction in the rate of neonatal hypoglycemia.A reduction in the rate of neonatal hyperbilirubinemia.A reduction in that rate of neonatal special care nursery or intensive care admission.A reduction in maternal and neonatal length of stay.A decrease in the time to conception.An increase in live birth rate.No difference in maternal gestational weight gain.

## Methods/design

A two-arm, parallel group, randomized control trial will be conducted in the Metabolic Disorders Centre, University of Melbourne. Obese (BMI 30–55 kg/m^2^) women planning pregnancy in the next 6–12 months will be recruited using social media advertisements (Facebook®) and via referral from a Weight Control Clinic at a tertiary hospital.

Subjects who identify themselves as potential trial candidates will click on the Facebook® advertisement and will be directed to a secure study website. An online ‘Registration of Interest’ form will be completed. This will be received by the study co-ordinator and will trigger a phone screening to ensure that the subject is (a) planning pregnancy in the next 6–12 months (b) lives in reasonable proximity to study sites (c) meets the BMI criteria. Potential trial participants will be sent a participant information and consent form. If they wish to proceed, they will contact the study co-ordinator and a screening appointment will be booked.

At the screening visit, patients will be reviewed by a medical doctor. After signing the consent form, medical history and current medications will be recorded. A medical summary will also be sought from the local doctor. A physical examination will be performed including height, weight, waist circumference and blood pressure. Patients unsuitable for the study will be referred to a weight management clinic in a tertiary hospital.

Inclusion criteria are women who meet the following:BMI 30–55 kg/m^2^18–38 years of agePlanning pregnancy in the next 6–12 monthsWilling to undergo a weight loss program and to avoid pregnancy during this program (16 weeks).Living in Victoria, Australia.

Exclusion criteria are:BMI < 30 and > 55 kg/m^2^Age < 18 and > 38 years oldCurrent pregnancy/lactationSignificant medical or psychiatric illness that would preclude the use of a VLED for 12 weeksCurrent use of drugs/complementary medicines known to impact weightDiabetes (Type 1 Diabetes or Type 2 Diabetes)Diabetes therapies (except Metformin). Metformin use in the context of Polycystic Ovarian Syndrome (PCOS) is not an exclusion. However, participants will be asked to with-hold the dose on the day before all study blood tests. Participants are not permitted to up-titrate the dose of Metformin for the duration of the study. The dose may be ceased if medically indicated.Discretion of the investigator

Withdrawal criteria are:The participant wishes to discontinueThe participant is unwilling or unable to comply with the study protocol.The participant misses more than one trial visit during the weight loss phase of the study.The participant is pregnant before the completion of the weight maintenance phase. In this case, the pregnancy will be followed but data will not be included in study results.The participant is withdrawn at the discretion of the investigator for a medical, psychological or social reason.

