### Statistical analysis/Power calculation

Most studies investigating the impact of maternal weight on pregnancy outcome have used the incidence of LGA neonates as the primary outcome. If this study used the same outcome, > 2000 women would be required to have sufficient offspring to achieve adequate power. This is clearly not practical. The HAPO data demonstrated a strong and continuous association between maternal fasting glucose at 24–32 weeks and pregnancy outcomes, including LGA neonates. Therefore, change in maternal fasting glucose at 26–28 weeks’ gestation can be used as a proxy for the incidence of LGA neonates.

In our pilot study, Phase 1 of the study demonstrated substantial weight loss (SWL) resulted in a reduction in maternal fasting glucose of approximately 10% (actual 9.12%, SE = 1.83, *n* = 24) compared to the modest weight loss (MWL) group (1.24%, SE = 1.40, *n* = 14). This is similar to previous studies by Sumithran [50] and Purcell [34]. In phase 3 of the pilot study (*n* = 10, MWL 3, SWL 7), glucose reductions were maintained at both 12 weeks’ gestation and 26–28 weeks’ gestation in both groups. Allowing for at least a moderate effect size of 0.6 for difference in percentage decrease in glucose at 26–28 weeks’ gestation (i.e. difference in means = 6, SD = 10; or slightly larger difference in means and larger SD) we require 45 women in each group to achieve 80% power.

We anticipate 45% of participants will not achieve a live birth within the study time-frame. This would include 20% drop-out during the weight loss phase. The anticipated drop-out rate is based on pilot data, on previous studies conducted by Purcell [34] and Rothberg [61], and by the lifestyle interventional study conducted by Mutsaerts [17]. We anticipate a further 25% of participants will fail to become pregnant within 12 months or will experience an early pregnancy loss at < 20 weeks’ gestation. This is based on the data from Kort et al. who found women with a mean BMI of 36 kg/m^2^ had a conception rate of 88% or 54% when losing ≥ 10% weight or < 10% weight, respectively [28]. We therefore require approximately 164 individuals.

The primary outcome will only consider those women who conceive and have a 75 g Oral Glucose Tolerance Test at 26–28 weeks’ gestation. Where appropriate, secondary outcomes will be analyzed both considering only those women conceive and also by intention to treat.

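### Pregnancies that begin before the end of week 16 are followed but left out of the results, which contradicts the intention-to-treat analysis of time to conception and live birth

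*Protocol article*

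**What the plan says.** The withdrawal criteria in Methods/design list five reasons for withdrawal. One is: "The participant is pregnant before the completion of the weight maintenance phase". It is the only one followed by a rule about data: "In this case, the pregnancy will be followed but data will not be included in study results". Under Phase 2 of the intervention, weight maintenance ends at week 16, after which women may stop contraception. The rule applies to both groups.

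The Aim section lists a shorter time to conception and a higher live birth rate among the secondary aims. Statistical analysis/Power calculation then states: "Where appropriate, secondary outcomes will be analyzed both considering only those women conceive and also by intention to treat". The primary outcome is handled separately: "The primary outcome will only consider those women who conceive and have a 75 g Oral Glucose Tolerance Test".

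Outcome measures says that the 26–28 week glucose tolerance result is collected in all participants, with one exception (a positive early test), and that the maternity record is obtained for all women who become pregnant. Neither statement excepts early pregnancies.

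On safety, the Background discusses the worry that a VLED exposes the fetus to ketosis and concludes: "Hence, the early developing fetus would only be exposed to ketosis if unintended pregnancy occurred". The Discussion looks ahead to evidence that the program is safe and could change guidelines.

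**The concern.** Pregnancy before week 16 happens after randomisation. For time to conception it is the outcome event, and for live birth it is the necessary step towards it. Leaving out the women in whom it occurs is not intention to treat. It selects on the outcome.

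The selection need not be balanced. The Background expects VLED weight loss to improve fertility, and the power section cites a study with conception rates of 88% and 54% in women losing at least 10% and less than 10% of body weight. If more early conceptions occur in the substantial weight loss arm, the rule removes more events from that arm and understates its effect on these outcomes. If they occur more often in the other arm, the bias runs the other way.

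Separately, the rule withholds from the results the only pregnancies in the trial that bear on the ketosis question.

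**Working it through.** **1. Who is removed, set against what is promised.**
- Withdrawal criteria: pregnancy by week 16, either arm; followed, but data left out of the results.
- Statistical analysis: secondary outcomes by intention to treat, where appropriate. Time to conception and live birth are defined for every randomised woman, so the approach is plainly appropriate for them.
- Outcome measures: test results and maternity records are gathered with no exception for early pregnancy.

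The first statement cannot hold together with the second for these two outcomes. An early-pregnant woman with a 26–28 week test also fits the stated primary analysis set, yet the withdrawal rule takes her out of the results.

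**2. The plan's own figures.** With a difference of 6 and SD of 10 (two-sided 5% level, equal allocation and 80% power; the first two are my assumptions), the normal approximation gives 2 × (1.96 + 0.84)² × (10/6)² ≈ 43.6, so 44 per group. The t-test gives 44.6, so 45, as stated. Then 90/(1 − 0.45) = 163.6, so 164, as stated. Per arm this is 164/2 = 82 women, with 82 × 0.55 ≈ 45 expected live births.

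**3. Illustration for live birth rate.** Assumptions: N = 82 per arm; L = 45 live births per arm from later pregnancies, set equal to isolate the effect of the rule; k early pregnancies; a share p = 0.80 of them ending in live birth. The documents give neither k nor p, nor do they say how excluded women enter the denominator, so both possibilities are shown.

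- All randomised: (L + kp)/N
- Early pregnancies dropped from the denominator: L/(N − k)
- Early pregnancies counted as no live birth: L/N

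| k in Group A, Group B | All randomised, A vs B (B − A) | Dropped, A vs B (B − A) | Counted as failure (B − A) |
|---|---|---|---|
| 0, 4 | 54.9% vs 58.8% (3.9) | 54.9% vs 57.7% (2.8) | 0 |
| 4, 8 | 58.8% vs 62.7% (3.9) | 57.7% vs 60.8% (3.1) | 0 |
| 4, 4 | 58.8% in both (0) | 57.7% in both (0) | 0 |
| 8, 4 | 62.7% vs 58.8% (−3.9) | 60.8% vs 57.7% (−3.1) | 0 |

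For example, in the first row Group B has (45 + 4 × 0.8)/82 = 48.2/82 = 58.8% with all women kept, and 45/78 = 57.7% with four dropped.

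Sensitivity to p: with 0 versus 4, the all-randomised difference is 4p/82. It is 4.9 points at p = 1. At p = 45/78 = 57.7% it is 2.8 points, and only there does dropping the women leave the difference unchanged. When numbers are equal in the two arms, the difference is unaffected but the rates are too low.

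**4. Time to conception.** A woman who conceives by week 16 has a known, short time. Dropping her loses an event. Censoring her at withdrawal censors her because of the event itself, which is fully informative. Neither gives an intention-to-treat comparison.

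**5. Safety.** The VLED runs over weeks 0–12 and the exclusion runs to week 16. Every pregnancy conceived on the study VLED therefore lies inside the excluded set. The set is wider than that: it also holds Group A pregnancies and those conceived in weeks 13–16.

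**The case against.** The strongest reply is that the problem may be small. Women agree to avoid pregnancy for 16 weeks, are asked to use contraception and have regular pregnancy tests, so there may be few early pregnancies. They are also followed, and serious adverse events are reported as ethics committees specify. This stands as a limit on size. It does not remove the contradiction, and event reporting is no substitute for showing these pregnancies by arm. Fetal safety of ketosis is not a listed aim, but the Discussion's hoped-for conclusion relies on it.

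Four stronger readings are tempting, and the article does not support them.

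- A reader might infer that the withdrawal rules as a whole discard randomised women. Only the pregnancy criterion states a data exclusion. The criteria for non-compliance and for missed visits ("The participant misses more than one trial visit during the weight loss phase of the study") are silent on data use, which a fuller document may settle, and they are not part of this point.
- A reader might infer that intention to treat has become impossible. The pregnancies are followed, so the analysis can be done once the rule is changed. Nor was it promised for the primary outcome, whose restriction is declared openly.
- A reader might suppose that drop-out is heavier on the VLED because it is harder to follow. Nothing in the text says so; the Background says rapid loss helps engagement. Only the fertility argument for an imbalance has support.
- A reader might expect a power gain from keeping women who leave the diet. Suppose 20% of 164, about 33 women, left and 40–71% of them conceived (assumed). That adds 13–23 results to the 90, and power reaches 85–89% only if those women show the full effect of 0.6. With no effect in them, the standardised difference falls to 0.6 × 90/103 ≈ 0.52 or 0.6 × 90/113 ≈ 0.48, and power to about 75% or 71%. The article does not attribute that drop-out to early pregnancy, so no gain is claimed.

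**Conclusion.** The point holds for the early-pregnancy rule. As written, it contradicts the intention-to-treat analysis of time to conception and live birth by excluding women because they conceived, and it keeps all VLED-conceived pregnancies out of the results.

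Its size cannot be fixed from the document. In the illustrations, an imbalance of four early pregnancies distorts the live-birth difference by 0.8 to 1.1 points if the women are dropped (3.9 − 3.1 and 3.9 − 2.8), and by 3.9 points if they are counted as failures. These figures rest on the assumed counts, on 45 later live births in each arm and on 80% of early pregnancies ending in live birth. If the counts are equal, the comparison is unbiased and only the rates shift. The safety gap does not depend on any of these assumptions.

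**What to change.** Reconcile the withdrawal criteria, Outcome measures and Statistical analysis/Power calculation as follows.

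- Remove the data exclusion for the intention-to-treat analyses. Whether an early-pregnant woman leaves the intervention is a clinical matter and is not in question here; the change concerns only her data.
- Keep every randomised woman in her assigned arm for live birth and time to conception, with time counted from randomisation.
- Report pregnancies that begin by week 16, and their outcomes, by arm as safety data.
- Use the set without early pregnancies only as a per-protocol or conditional sensitivity analysis.
- State explicitly whether an early-pregnant woman with a 26–28 week test enters the primary analysis, since the sections now disagree.

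The cost is a change of wording and some extra tabulation, because these pregnancies are already followed. The estimated effect may be slightly diluted by women who conceived before completing the program, which the sensitivity analysis will show. The sample size of 164 does not change.
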